### Randomization

Using stratified block randomization (block size of 6) [21], participants are assigned into 1 of the 2 equal-size age-, sex-, and severity-matched groups: group 1 and group 2 (Table 1). Balanced randomization is applied within each block, such that 3 participants receive the active transcranial alternating current stimulation treatment and the rest receive the sham treatment. This randomization procedure is used to avoid bias in statistical analyses comparing the 2 groups.

**Table 1 table1:** Stratified blocks using 2 levels for 3 factors.

Block number	Factor		
	Age (years)	Sex	Severity (Montreal Cognitive Assessment score)
1	≥70	Female	≥18
2	≥70	Female	<18
3	≥70	Male	≥18
4	≥70	Male	<18
5	<70	Female	≥18
6	<70	Female	<18
7	<70	Male	≥18
8	<70	Male	<18

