### Treatment Protocol

Training for all groups occurs in-person over the course of 4 weeks, 5 days per week (excluding weekends); there is an 8-week wash-out period prior to group crossover. On each day, participants attend two 30-minute training sessions using an app (MindTriggers) with a 30-minute break in between. Assessments occur at baseline (week 0), postintervention (weeks 5 and 11), at a follow-up (week 16), and at a long-term follow-up (week 27). Assessment at week 11 is considered to be baseline for the second cycle. No crossover occurs for participants assigned to group 3 (Figure 1).

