### Analysis

Both parametric and nonparametric statistical techniques will be used. Analysis of the repeated measures crossover data will be performed using fixed and random effect models to investigate different sources of variations in the data set such as period effect, direct treatment effect, and carryover treatment effects [36]. If raw data are found to not be normally distributed, the Box-Cox transformation will be employed to satisfy the normality assumption needed to perform the analysis [37].

In addition, the differences between study cycle data of the basic crossover design will be analyzed (that is, the differences between active and sham transcranial alternating current stimulation results). Study cycle data differences are used to transform the repeated measurements crossover design to a completely randomized repeated measurements design. With the transformed repeated measurements completely randomized design, analysis is completed by a univariate split-plot analysis of variance or multivariate (over time) *F* tests [38]. Should normality be in question due to the relatively small sample size, an alternative approach will be used based on nonparametric tests using ranks [39]. Nonparametric tests will include Wilcoxon rank sum and permutation tests to investigate hypotheses 1 and 2 and examine the absence of carryover effects in the study [39].

To have a better understanding of the data set, baseline measurements will be used to perform analysis of covariance. As such, the baseline crossover differences of each outcome measure (Table 2) are regarded as independent explanatory variables and regression of the basic estimators is calculated on said variables [36].

The abovementioned statistical analysis will be applied to the secondary outcome measures, as well.

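### The cycle difference has no stated order of subtraction; on one reading of the protocol's gloss, the between-group test measures the period effect instead of the treatment effect

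*Protocol article*

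**What the plan says.** The trial is a two-group, two-cycle crossover. Within each block of six, "3 participants receive the active transcranial alternating current stimulation treatment and the rest receive the sham treatment" first (Randomization), and "there is an 8-week wash-out period prior to group crossover" (Treatment Protocol).

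The Analysis section first plans fixed and random effect models covering period, direct treatment and carryover. It then adds a second approach, in which "the differences between study cycle data of the basic crossover design will be analyzed". A bracketed gloss explains these as "that is, the differences between active and sham transcranial alternating current stimulation results". The next sentence reads: "Study cycle data differences are used to transform the repeated measurements crossover design to a completely randomized repeated measurements design". The parametric test follows: "analysis is completed by a univariate split-plot analysis of variance or multivariate (over time) *F* tests". If normality is in doubt, ranks are used: "Nonparametric tests will include Wilcoxon rank sum and permutation tests to investigate hypotheses 1 and 2". Hypothesis 1 is the comparison of active with sham periods (Hypotheses).

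The section does not say which cycle or treatment is subtracted from which.

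**The concern.** After differencing, each participant contributes one difference, or one profile of differences over time. The only randomized factor left between participants is the sequence, Group 1 (active first) v Group 2 (sham first). A completely randomized design on these differences therefore implies a comparison of the two sequences, and so does a two-sample rank sum test.

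What that comparison tests depends on the sign convention. The phrase about study cycles suggests cycle 1 minus cycle 2. The gloss, taken alone, suggests active minus sham for everyone. In Group 1 these are the same number; in Group 2 they have opposite signs. An analyst who codes the gloss as active minus sham and then compares the groups would have a test that cannot see the treatment effect and would read a period effect as a group effect.

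**Working it through.** **Inputs**

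- From Sample Size Estimation: difference 20, SD 38, power 80%, significance 5%, 58 per group before halving, 5% dropout, 20% intolerance, 75 enrolled.
- Assumed: two-sided testing; SD 38 applies to each cycle's outcome; the correlation r between a participant's two cycles, which the protocol does not give, is 0 or 0.5; period effects of 10 and 20 points, chosen for illustration.

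**The protocol's own figure**

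The normal approximation gives n = 2 × (1.96 + 0.84)² × 38² / 20² = 56.7, so 57 per group. The noncentral t gives 58 per group (power 0.802), which matches the stated figure. Enrolment of 75 leaves 75 × 0.80 × 0.95 = 57 participants, or 29 v 28. The sample size does not depend on this point.

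**Expected differences**

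Let t be the treatment effect and p the cycle-1-minus-cycle-2 effect, with no carryover.

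| Difference | Group 1 (active first) | Group 2 (sham first) | Group 1 minus Group 2 | Mean of the two groups |
|---|---|---|---|---|
| Active minus sham | t + p | t − p | 2p | t |
| Cycle 1 minus cycle 2 | p + t | p − t | 2t | p |

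The same data answer different questions. Under active minus sham, treatment sits in the average of the two group means and period in the group contrast. Under cycle 1 minus cycle 2 the roles are exchanged. These expectations hold at any correlation.

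**Size of the effect**

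The SD of a difference is 38 × √(2(1 − r)). The standard error of the group contrast is that SD × √(1/29 + 1/28) = SD × 0.265.

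- r = 0: SD 53.7, SE 14.2
- r = 0.5: SD 38.0, SE 10.1

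Rejection rates for a two-sample t test at two-sided 5%, 55 degrees of freedom (noncentral t):

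| Setting | r | Active minus sham, between groups | Cycle 1 minus cycle 2, between groups |
|---|---|---|---|
| t = 20, p = 0 | 0 | 5% | 79% (40 / 14.2 = 2.81) |
| t = 20, p = 0 | 0.5 | 5% | 97% (40 / 10.1 = 3.97) |
| t = 0, p = 10 | 0 | 28% (20 / 14.2 = 1.40) | 5% |
| t = 0, p = 10 | 0.5 | 50% (20 / 10.1 = 1.99) | 5% |
| t = 0, p = 20 | 0 | 79% | 5% |
| t = 0, p = 20 | 0.5 | 97% | 5% |

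A simulation with 29 per sequence, r = 0.5 and 10,000 runs agrees. With t = 20 and p = 0, active minus sham compared between groups rejects in 4.8% of runs and cycle 1 minus cycle 2 in 97.8%. Testing the equally weighted mean of active minus sham against zero also rejects in 97.8%.

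**Carryover**

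Adding a carryover of 10 points from active into cycle 2 (t = 20, p = 0) moves the active-minus-sham contrast to about −10, so that contrast mixes period and carryover. It also lowers the cycle 1 minus cycle 2 contrast from 40 to about 30, so half of it is 15 instead of 20. The valid form still relies on the wash-out.

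**The case against.** A reader might infer that the protocol specifies the wrong test outright. The text does not support that, for two reasons.

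- No subtraction is written. The main phrase, used twice, is a difference between study cycles. Cycle 1 minus cycle 2 is also a difference between active and sham results for every participant, with the sign reversed in Group 2. That reading satisfies both phrases, fits the completely randomized design, and is the valid analysis.
- The protocol does not say which effect in the split-plot or multivariate analysis is the treatment test. Active minus sham can still test treatment through the average of the two group means. The rank sum test leaves less room, because it is a two-sample test and is named for hypothesis 1.

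A reader might also infer that the trial would have no usable treatment analysis. That does not follow either: the first-listed models include period and direct treatment, and the difference analysis is an addition to them.

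Two further objections bear on size. The primary outcomes are changes from baseline, and week 11 serves as a new baseline for cycle 2 (Outcome Measures; Treatment Protocol). Stable shifts in level between cycles therefore largely cancel, and p is only the difference in within-cycle change. Alternate ADAS word lists also limit practice effects on that scale. So the protocol does not establish a large period effect, and the 10- and 20-point values are illustrative only. This weakens the false-positive side of the concern but not the loss of power, which occurs even when p is zero.

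Finally, sign coding is often left to an analysis plan, and the cited method sources may settle it. But here the article offers a definition of its own, and that definition leaves open the choice that determines the test.

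**Conclusion.** The point holds as an ambiguity with a material consequence. The two descriptions of the difference agree only up to a sign in one sequence group, and that sign determines whether the between-group test addresses treatment or period. On the unfavourable reading, power for a 20-point effect falls from about 79% (assumed correlation 0) or 97% (assumed correlation 0.5) to the 5% significance level. These rates assume an SD of 38 per cycle, 29 v 28 participants and no carryover; the cancellation itself does not depend on the SD or the correlation.

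The scope is the additional difference-based and rank analyses, which the section also extends to the secondary outcomes. The fixed and random effect models are not affected. Severity is moderate to minor.

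**What to change.** Replace the bracketed gloss with a definition: the difference is cycle 1 minus cycle 2 for every participant. State that it is compared between the two sequence groups by the split-plot or multivariate F test, or by the rank sum test, and that half the group contrast is reported as the treatment effect.

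If active minus sham is preferred, state that treatment is tested by the equally weighted mean of the two sequence means, and label the between-group test as the test of period. In that case the rank sum comparison of the groups cannot be the test of hypothesis 1.

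The cost is one sentence. It needs no new data and no change to the sample size.

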### Hypotheses

We hypothesize that (1) better cognitive performance will be evident for patients’ active treatment periods compared with those from the sham periods; (2) in both groups, statistically significant improvement in cognitive performance will be evident immediately postintervention compared with baseline, and (3) a statistically significant difference in cognitive improvement will be found between the active and sham transcranial alternating current stimulation groups.

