### Outcome Measures

At each assessment, 9 tests are conducted over 2 days due to time constraints. The first assessment day comprises the Wechsler Memory Scale Older Adult Battery [27], Montgomery-Åsberg Depression Rating Scale, a verbal fluency test for speech analysis, a visual 1-back task [28], virtual reality navigation [29], the Neuropsychiatric Inventory Questionnaire, and functional near-infrared spectroscopy. The second assessment day includes electrovestibulography and the Alzheimer Disease Assessment Scale (ADAS) cognitive subscale. An assessor is assigned to each participant and performs all 4 assessments with the assigned participant. Only the study participant and the research personnel designated to administer assessments are present during assessments.

The primary outcomes are the changes in patients’ scores from baseline in the Wechsler Memory Scale Older Adult Battery and ADAS cognitive subscale assessments. Alternate forms of the ADAS cognitive subscale word lists are employed at each visit to reduce possible practice effects. The secondary outcomes are change in 1-back, Neuropsychiatric Inventory Questionnaire, and Montgomery-Åsberg Depression Rating Scale performance. The 1-back test presents a sequence of random shapes and participants must recall whether a presented object is a repeat of the previous object [28]. Neuropsychiatric Inventory Questionnaire is used to assesses neuropsychiatric symptoms and caregiver burden. Finally, to establish the presence of confounding variables, namely mood disorders, Montgomery-Åsberg Depression Rating Scale is evaluated at each assessment. The secondary exploratory outcome measures use a series of physiological monitoring tools to examine physiological changes in study participants before and after the intervention: (1) virtual reality navigation test to assess spatial orientation [29], (2) electrovestibulography [30-32] to assess static and dynamic vestibular response, (3) functional near-infrared spectroscopy (OctaMonas) [33] to record prefrontal cortex brain activities, and (4) verbal fluency to evaluate acoustic and linguistic changes (Table 2). It should be noted that the exploratory assessments will only be conducted at the Manitoba site.

**Table 2 table2:** Study outcome measures.

Outcome measures		Assessments

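### Wilcoxon rank sum, an independent-samples test, is named for the before-after hypothesis 2, and no paired rank test is named; secondarily, the Box-Cox trigger looks at raw data rather than model residuals

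*Protocol article*

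**What the plan says.** The Hypotheses section sets out three claims. Hypothesis 1 is that "better cognitive performance will be evident for patients’ active treatment periods compared with those from the sham periods". Hypothesis 2 is that "in both groups, statistically significant improvement in cognitive performance will be evident immediately postintervention compared with baseline". Hypothesis 3 is that the improvement differs between the active and sham groups.

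The Analysis section plans fixed and random effect models for the crossover data, and then an analysis of the differences between cycles. Two provisions deal with non-normality:

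- A transformation: "If raw data are found to not be normally distributed, the Box-Cox transformation will be employed to satisfy the normality assumption".
- A rank-based alternative for when the small sample puts normality in doubt: "Nonparametric tests will include Wilcoxon rank sum and permutation tests to investigate hypotheses 1 and 2". The same tests are also to serve as the check on carryover.

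No signed-rank or other paired rank test is named. The same methods are extended to the secondary outcomes. Under Outcome Measures, the primary outcomes are defined as changes: "The primary outcomes are the changes in patients’ scores from baseline" on the two named scales.

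**The concern.** Hypothesis 2 has no between-group element. Within each group it sets two measurements on the same people against each other. Rank sum takes its null variance from two independent samples. When the two measurements are positively correlated, as repeated memory scores in one person normally are, the difference between visits varies less than that null variance allows. The test then rejects too rarely. A true improvement could be reported as not significant because of the choice of test.

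The Box-Cox provision raises a smaller question. The normality assumption of a mixed model concerns its residuals and random effects. Raw scores pooled over a population with Montreal Cognitive Assessment scores from 5 to 24, stratified at 18, can look non-normal while the residuals are well behaved. The check could therefore trigger a transformation that the model does not need.

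**Working it through.** **Inputs from the documents.** Sample Size Estimation gives a difference of 20, SD 38, power 80%, significance 5%, 58 per group before halving for the crossover, and 75 enrolled in total.

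**Assumptions.** Tests are two-sided. SD 38 applies to the score at each visit. Scores are bivariate normal. The pre-post correlation ρ is not in the documents, so it is varied from 0 to 0.9.

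**Step 1: the plan's own figure.** By the normal approximation, n = 2(1.96 + 0.84)² × 38² / 20² ≈ 56.7, so 57 per group. The t-based calculation gives 57.6, so 58. The stated 58 is reproduced. Halving gives 29 per sequence. For the total, 57/(0.95 × 0.80) = 75.0 and 58/(0.95 × 0.80) = 76.3, both consistent with 75.

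**Step 2: why rank sum is conservative on paired data.** For the difference of two means, an independent-samples test uses variance 2σ²/n. The actual variance with pairing is 2σ²(1 − ρ)/n. The standardized statistic therefore has SD √(1 − ρ) under the null, and the actual type I error is roughly 2Φ(−1.96/√(1 − ρ)):

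- ρ = 0.3: 2Φ(−2.34) ≈ 1.9%
- ρ = 0.5: 2Φ(−2.77) ≈ 0.6%
- ρ = 0.7: 2Φ(−3.58) ≈ 0.03%

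**Step 3: simulation of the rank tests themselves.** 10,000 runs, 29 pairs, SD 38, nominal 5%. Each cell shows rank sum v signed-rank.

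| ρ (assumed) | Type I error | Power, 10-point gain | Power, 20-point gain |
|---|---|---|---|
| 0 | 0.047 v 0.047 | 0.16 v 0.15 | 0.48 v 0.47 |
| 0.3 | 0.018 v 0.046 | 0.12 v 0.20 | 0.48 v 0.62 |
| 0.5 | 0.008 v 0.047 | 0.08 v 0.26 | 0.48 v 0.76 |
| 0.7 | 0.001 v 0.050 | 0.05 v 0.41 | 0.48 v 0.93 |
| 0.9 | 0.000 v 0.047 | 0.01 v 0.85 | 0.51 v 1.00 |

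The two tests agree only when ρ = 0. The 20-point figure is the plan's between-group difference, borrowed here as a yardstick. The plan states no expected within-group gain.

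**Step 4: if both sequences were pooled (58 pairs).** Rank-sum type I error for ρ = 0.3 to 0.9 is again 0.019 falling to 0.000. Power for 20 points is 0.82 v 0.90 at ρ = 0.3 and 0.92 v 1.00 at ρ = 0.7. For 10 points at ρ = 0.7 it is 0.15 v 0.70. The loss at 20 points is smaller, but the fault is the same.

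**Step 5: hypothesis 1.** Rank sum was applied to period differences between the two sequences (29 each, within-person correlation 0.7, a 10-point period effect). Simulated type I error was 0.050. The misfit is confined to hypothesis 2.

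**Step 6: Box-Cox and change scores.** Box-Cox needs strictly positive values. The SD of a change is 38√(2(1 − ρ)), which is 38.0, 29.4 and 17.0 for ρ = 0.5, 0.7 and 0.9. With a mean gain of 20, the share of changes at or below zero is Φ(−20/38.0) = 30%, Φ(−20/29.4) = 25% and Φ(−20/17.0) = 12%. With no mean gain it is 50%. These shares matter only if the transformation is applied to changes.

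**The case against.** The sentence does not pair tests with hypotheses one by one, its list is open-ended, and it also names permutation tests, which can be run in paired, sign-flip form. Rank sum is a proper choice for hypothesis 1 and for carryover, and the text has just reduced the crossover to cycle differences. A full protocol or analysis plan may make the assignment clear. This lowers the severity but does not remove the point: as written, rank sum covers hypothesis 2, and a permutation test that shuffles scores as if they were independent would share its fault. If rank sum was meant for change scores compared between groups, that answers hypothesis 3, and the sentence still needs correcting. Its silence on hypothesis 3 does little harm in itself, since hypotheses 1 and 3 both compare active with sham and can share a test.

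On Box-Cox, a reader might infer that the transformation is undefined for much of the data because the outcomes are changes. The documents do not support that as the main reading. The provision speaks of raw data and directly follows the model for the repeated-measures crossover data, so visit scores are the more natural meaning, and the shares in step 6 then do not apply. Nor can both complaints be pressed at full strength together: if changes were transformed, much of the between-patient spread that might upset a raw-data check would already have been differenced out. Planning a transformation in advance is conventional, and removing it would be a preference rather than a correction.

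**Conclusion.** The point holds in a limited form. The test named for hypothesis 2 does not match paired data. With 29 pairs, it would run at about 2% to 0% type I error instead of 5%, and for a 20-point gain would have about 48% to 51% power where signed-rank has 62% to 100%. These ranges rest on an assumed correlation of 0.3 to 0.9, SD 38 at each visit, normal data and two-sided testing. The direction is the same at every positive correlation tried; the size depends heavily on which one is true.

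The error is lost power, not false positives. It arises in a fallback used only when normality is in doubt, and in a within-group comparison that has no control. A reader might infer that the active-sham comparison or the trial's main conclusion is undermined. The documents do not support that, because rank sum on cycle differences between sequences keeps its level.

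Of the Box-Cox provision, only one minor correction survives: normality should be judged on model residuals, not raw data.

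**What to change.** In the Analysis section:

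1. For hypothesis 2, name the Wilcoxon signed-rank test, or a sign-flip permutation test, on post-minus-baseline differences within each group.
2. For hypotheses 1 and 3, keep rank sum or permutation tests, stated as comparisons of cycle differences between the two sequences.
3. For carryover, state that rank sum or permutation tests compare subject totals between sequences.
4. Base the normality check on model residuals. If a Box-Cox transformation is then used, also report the result on the original score scale, on which the 20-point difference was set.

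The cost is wording only: no extra data, visits or participants. The article reports 7 participants enrolled as of February 10, 2022, so at that stage the change could be made well before analysis.

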### Ethics

Only participants able to give informed consent are recruited into the study. However, because the study population contains those with memory problems, a family member (or legal guardian) will be required to accompany the patient to the initial interview and sign the consent form for all participants.

Should a patient with Alzheimer disease be unable to provide informed consent, the person’s guardian, or an authority or other person having that responsibility at law, is required to provide consent to participate in the research on the individual’s behalf. Patients are advised that their participation is voluntary and that they are free to withdraw from the study at any stage.

Study data (participant medical and demographic data, treatment records, and assessment results) are maintained on a password-protected database accessible only to active research team members. All participants are assigned code numbers to ensure anonymity, with study files referencing participant code only. Regular backups of the database are performed and stored on a secure server. Identifying information (name, phone number, address) is not stored on the same system as study data and remains accessible only to staff members who need to contact participants.

Ethical approval for this study was received from the Biomedical Ethics Research Board at the University of Manitoba prior to participant recruitment at the Manitoba study location (HS25171 [B2021:089]). All participants or their legal guardians provide informed consent during the study.

